#### Self-reported questionnaires

We will also collect the following additional questionnaires to describe our patient population: ODI^57^ (separate questionnaires for back and leg), Keele Start Back tool,^58^ EQ-5D^59^ and a monthly pain diary (online supplemental appendix 3).

#### Magnetic resonance neurography

We will perform magnetic resonance neurography (MRN) in a subset of n=100 patients with sciatica and n=44 healthy matched controls to identify moderate effects^23^ (d=0.52, alpha=0.05, 80% power). Eligible patients (eg, MRI safety) will be consecutively recruited for scanning until numbers are reached.

We will perform advanced MRN optimised to visualise lumbar nerve root macrostructure and microstructure at 3 Tesla using a dedicated 18-channel phased array spine coil (Siemens, UK). The protocol includes multishell (b=700 and 1500 s/mm^2^) diffusion tensor imaging (DTI) scans, high-resolution anatomic scans with optimised T1 and T2-weighted contrasts, and a T2 mapping scan (DOI: 10.5281/zenodo.7760905). The data analysis will be performed using functional magnetic resonance imaging of the brain software library (FSL) tools including TOPUP^60 61^ and EDDY^62–64^ for the correction of images’ distortions and subject movements, DTIFIT^65^ for the fitting of diffusion tensor model and FLIRT^66 67^ for the registration of diffusion metrics and anatomic images. Measures including fractional anisotropy, mean/axial/radial diffusivity and T2 maps will be obtained within regions of interest in lumbar nerve roots (affected and unaffected sides) and averaged over multiple slices as we have optimised before.^68^

### Cohort harmonisation

The FORECAST cohort is harmonised with the Advanced Pain Discovery Platform funded PAINSTORM consortium, and, therefore, includes additional measures that will allow data integration (eg, blood collection for genetic analyses, skin biopsies in the maximal pain area, DN4,^69^ Michigan Neuropathy Screening Instrument,^70^ Chronic pain grade,^71^ Brief pain inventory^72^ (pain intensity items), a section where patients can tell us more about their pain and circumstances in their own words including how they would describe their pain to their friends/family or work colleagues as well as their feelings about their financial situation and its impact on their situation. This harmonisation may also enable external validation of the FORECAST findings in other neuropathies.

### Data analysis plan

Statistical methods will follow STROBE guidelines^17^ and the TRIPOD statement for ransparent reporting of a multivariable prediction model for individual prognosis or diagnosis.^18^

Participants’ baseline characteristics (eg, demographics, pain severity, disability, medical comorbidities) and their clinical course (primary and secondary outcomes, ODI) will be described for short (3 months) and long-term time points (12 months).

To identify and characterise mechanism-based subgroups in patients with acute/subacute sciatica and use distance-based clustering algorithms efficiently we first need to address the high dimensionality—modest sample size of the data set. Thus, we will first carry out a principal component analysis to summarise and reduce the dimensionality of the dataset while preserving as much variability as possible. Then we will use algorithmic centroid (k-means) and hierarchical clustering based on the Euclidean distance between principal dimensions to identify subgroups of patients sharing high phenotypic similarities. The optimal number of clusters will be determined using the gap statistic and the elbow of the within/between clusters variance plot. Consequently, we will perform hypothesis testing to assess group differences on the original variables between participants assigned to different clusters. All omnibus tests will be followed up by the appropriate post hoc test.

To investigate factors that predict pain persistence in people with sciatica, we will use variable selection techniques followed by predictive modelling. First, we will perform filtering of the original variables by calculating the univariate associations (coefficients, 95% CI, p values) between variables and the outcome and between each other. We will select a subset of uncorrelated variables that are associated with the outcome and use them as input features in machine learning algorithms for high-dimensional, small data sets that will allow us to identify the most powerful predictors and assess model selection/predictive accuracy. During preprocessing, missing data will be examined, the mechanism of missingness will be inferred using hypothesis testing and visually assessed using a matrix of boxplots for all pairs of variables and the outcome, and, if appropriate, multiple imputation by chained equations will be used. Drawing from machine learning techniques for high-dimensional small data sets, we will use resampling and validation in the form of repeated cross-validation to perform a complete variable profiling to identify the most powerful predictors. Multivariate adaptive regression splines (MARS) with built-in feature selection and Decision Tree models known to work well on low sample sizes will be trained to predict the 3-month and 1-year outcome. Model performance will be estimated using five times repeated 10-fold cross-validation and compared with models trained on surrogate data.^73^ The latter benchmarking technique is appropriate for small data sets, where holding out a subset of data before the analysis to be used as a pseudo-independent test set is impossible. Instead, an artificial—surrogate data set, preserving the descriptive statistics but not any of the potentially real associations between the variables and the outcome of the original dataset, will be created and the performance of models trained on the actual and surrogate dataset will be compared. Models’ predictive performance will be reported alongside variable importance rankings. Model selection will be done to maximise the Mathews correlation coefficient for dichotomised outcomes and to minimise the root mean square error for continuous outcomes during cross-validation. Scalar metric estimations of predictive performance including accuracy (binomial test p value against the majority class prevalence), balanced accuracy and the area under the precision/recall curve will be reported alongside their 95% CI. Predictor importance will be assessed using model specific techniques, that is, the reduction in performance estimated by cross-validation when each predictor is removed for MARS and node impurity for tree-based methods. Variables’ influence on the predicted outcome both at the global and individual level will be quantified by the partial dependence plots and individual conditional expectation,^74^ respectively. These will show the average marginal effect on the prediction given a certain value of a predictor variable and provide model interpretability.

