### Participants

We will include n=180 patients with acute/subacute ‘sciatica’ and n=168 healthy age and gender-matched participants without symptoms of sciatica/LBP. Healthy participants are important to establish normative values for blood markers, somatosensory profiling and neuroimaging.

People aged >18 years with a clinical diagnosis of ‘sciatica’ will be recruited from primary care in Oxfordshire (eg, primary care providers for the National Health Service as wellGeneral Practitioners, Physiotherapy, Osteopathy and Chiropractor clinics) and through leaflets on public noticeboards. Sciatica symptom onset of the current episode needs to be within the past 3 months with a symptom-free period of at least 3 months preceding the current sciatica symptoms. The inclusion criteria for patients with ‘sciatica’ are based on a published diagnostic model,^19^ which includes five weighted parameters (self-reported sensory changes, below knee pain, leg pain worse than back pain, neurodynamic tests and neurological deficit). A sum score >4 will be defined as sciatica, with a mean predicted probability of 83%. In addition, patients with suspected sciatica will undergo a clinical examination by a physiotherapist to further confirm the diagnosis of sciatica and rule out other diagnoses (see the section additional phenotypic data below).

The following exclusion criteria will apply; presence of other nerve-related disorders (eg, diabetic neuropathy, stroke), previous lumbar spine surgery, serious spinal diseases (eg, infection, cauda equina syndrome, metastatic lesions), chronic inflammatory disorders, other pain conditions that may confound assessment (eg, fibromyalgia), pregnancy, insufficient command of the English language to obtain consent/complete questionnaires and contraindications to MRI for those selected for scanning.

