#### K-means and hierarchical clustering after PCA

Using the two first principal dimensions for three variable domains (self-reported profiling, QST, inflammatory markers), we will need 2^6^=64 patients to perform k-means clustering with adequate power.^77^

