#### Algorithmic cluster analysis

Assuming k=4 clusters, we will be able to identify moderate effects (effect size=0.25) with an one-way analysis of variance between four groups at an alpha level of 0.05, 80% power.

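### Clusters are tested for differences on the variables that formed them, so p values on the clustering inputs are not valid and the 80% ANOVA power applies only to variables left out of the clustering

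*Protocol article*

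**What the plan says.** All references are to the Protocol article.

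- **Forming the groups.** The Data analysis plan reduces the data by principal component analysis (PCA), then applies k-means and "hierarchical clustering based on the Euclidean distance between principal dimensions to identify subgroups of patients sharing high phenotypic similarities". The gap statistic and an elbow plot set the number of clusters.
- **Inputs.** The sample size section on k-means and hierarchical clustering after PCA describes them: "Using the two first principal dimensions for three variable domains (self-reported profiling, QST, inflammatory markers". That makes six dimensions.
- **Testing.** The Data analysis plan continues: "we will perform hypothesis testing to assess group differences on the original variables between participants assigned to different clusters". Every omnibus test is followed by a post hoc test.
- **Power.** The section on Algorithmic cluster analysis takes four clusters, a 5% alpha and 80% power, and describes what the study can do as follows: "identify moderate effects (effect size=0.25) with an one-way analysis of variance between four groups". No sample size is given there. The Participants section gives 180 patients.

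**The concern.** Clustering assigns patients to groups so that the groups lie apart on the component scores, which are weighted sums of the original variables. An ANOVA on one of those variables then tests a null hypothesis of equal means that the grouping itself has already broken. The F distribution behind the p value assumes groups fixed without reference to the tested variable, and the same assumption lies behind the power figure.

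The first aim is to explore mechanism-based subgroups, and these tests are the only inferential step the section gives for characterising them. A low p value on, say, a cytokine could be taken as showing that inflammation separates the subgroups when the algorithm alone produced the difference. The surrogate-data benchmark and the cross-validation are described only for the models that predict outcome, so they do not cover this step.

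**Working it through.** **1. Reproduce the stated power.** Inputs from the article: k = 4, effect size 0.25 (read as Cohen's f), alpha 0.05, N = 180. The test is F with k − 1 = 3 and N − 4 degrees of freedom, and noncentrality λ = N·f².

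- N = 180: λ = 180 × 0.0625 = 11.25; power 80.4%.
- The smallest N that reaches 80% is 179, or 180 with four equal groups of 45.

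The figure reproduces.

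**2. Error rate on clustering inputs when no subgroups exist.** From the article: N = 180, three domains, two components per domain, k = 4. Assumptions not in the article: multivariate normal data, 10 or 15 variables per domain, a common within-domain correlation of 0, 0.3 or 0.5, and independent domains. There were 200 replicates per setting, with a one-way ANOVA on each original variable at 0.05.

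| Method | Variables per domain | Correlation | Inputs rejecting | Rejecting after Bonferroni | Independent variable rejecting |
|---|---|---|---|---|---|
| k-means | 10 | 0 | 71.7% | 47.3% | 5.5% |
| k-means | 10 | 0.3 | 100% | 99.1% | 6.0% |
| k-means | 10 | 0.5 | 100% | 100% | 6.5% |
| k-means | 15 | 0 | 61.3% | 31.2% | 3.5% |
| k-means | 15 | 0.3 | 100% | 98.0% | 6.5% |
| k-means | 15 | 0.5 | 100% | 100% | 6.0% |
| Ward | 10 | 0 | 65.4% | 39.0% | 8.5% |
| Ward | 10 | 0.3 | 99.1% | 93.9% | 4.0% |
| Ward | 10 | 0.5 | 99.9% | 99.5% | 5.0% |
| Ward | 15 | 0 | 55.3% | 23.9% | 4.0% |
| Ward | 15 | 0.3 | 99.0% | 92.3% | 6.0% |
| Ward | 15 | 0.5 | 99.7% | 98.8% | 4.5% |

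At least one input was significant in every replicate. The independent variable averages 5.5% over the twelve settings (0.66/12), close to nominal.

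**3. Fewer clusters.** With 12 variables per domain, correlation 0.3, k-means and 100 replicates, the rejection rate on inputs was 74% at k = 2, 94% at k = 3 and 99.9% at k = 4.

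**4. One real split.** Two groups differ by 1.5 SD on the variables of one domain only; other settings are as in step 3. Variables in the other two domains, which have no true difference, rejected in 12.9% of tests at k = 2 and 98.6% at k = 4.

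**5. The gap statistic as a gate.** There were 30 data sets without clusters per setting, with k from 1 to 6.

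- Normal data: it returned k = 1 in 30 of 30 under both the one-standard-error rule and the maximum-gap rule.
- Log-normal data: k = 1 in 30 of 30 under the one-standard-error rule, but 3 to 6 clusters in 28 of 30 under the maximum-gap rule.

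**6. Power for variables outside the clustering** (same formula, k = 4, f = 0.25).

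- Outcomes after the 15% attrition used under Predictor profiling: N = 180 × 0.85 = 153; λ = 9.56; power 72.8%.
- MRN subset: N = 100; λ = 6.25; power 51.8%.

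**The case against.** **The plan already has a gate.** The gap statistic is applied before any testing and can return one cluster, in which case nothing is tested. This stands in part. The rates in steps 2 and 3 are conditional on more than one cluster being accepted, and a reader might wrongly infer that they are the error rate of the whole procedure. But the gap rule is not named, the elbow plot it is paired with cannot return k = 1, and step 5 shows that the choice of rule matters for skewed data. The gate also does not help once k exceeds 1, as step 4 shows.

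**The power statement might be called meaningless.** That goes too far. The arithmetic is right, and the section on Algorithmic cluster analysis does not say which variables the ANOVA will test. The link to the clustering inputs comes from the Data analysis plan. For a variable outside the clustering, measured in all 180 patients, the 80% keeps its usual meaning.

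**The work is exploratory, and no sentence says that the p values will prove the clusters exist.** Both are fair. A reader might infer that the subgroups themselves, or the prognostic analysis, are invalidated. The article does not support that. Cluster assignments and descriptive profiles survive, and cluster membership is not listed as an input to the outcome models. Exploratory status still does not make a circular p value interpretable.

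**Conclusion.** The concern holds for hypothesis tests on variables used to form the clusters. Their p values are not valid once more than one cluster is accepted. With no true subgroups and k = 4 imposed, 55% to 100% of input variables reject at a nominal 5%, and Bonferroni leaves 24% to 100%. With one real split confined to one domain, variables in the other domains reject about 13% of the time at k = 2 and 99% at k = 4, so the tests can attribute a subgroup to the wrong mechanism.

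The sizes depend on assumed normality, numbers of variables and correlations that the article does not give. The inflation appeared in every setting tried. It is also assumed that the three domains named in the sample size section are the clustering inputs.

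The 80% power is correct as arithmetic, but holds only for a continuous variable kept out of the clustering and observed in all 180 patients.

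**What to change.** 1. In the Data analysis plan, report the clustering inputs by cluster descriptively, with means and standardised differences and without p values or post hoc tests.
2. Restrict hypothesis tests to variables not used in clustering, such as the Sciatica Bothersomeness Index and pain rating at 3 and 12 months and the MRN metrics, with false discovery rate control across them.
3. Name the gap rule, state that it may return one cluster, and add a bootstrap check of cluster stability.
4. Restate the power under Algorithmic cluster analysis as applying only to continuous variables outside the clustering, at the number available. For f = 0.25 and k = 4 this is about 73% for outcomes at N = 153 and about 52% for MRN at N = 100. Claim no ANOVA power for categorical variables such as the neuropathic pain grade or the clinical examination subgroup.

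The cost is a change of wording in the analysis plan, with no new data. The study would report fewer p values and a less favourable stated power.

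### Predictors are screened against the outcome in all patients before cross-validation, so the reported cross-validated performance will be optimistic

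*Protocol article*

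**What the plan says.** The relevant text is the prediction paragraph of the Data analysis plan in the protocol article. It fixes the order of work: "we will use variable selection techniques followed by predictive modelling". The first step is stated as: "First, we will perform filtering of the original variables by calculating the univariate associations". The result of that step feeds the learners: "We will select a subset of uncorrelated variables that are associated with the outcome and use them as input features in machine learning algorithms". The learners are MARS and decision trees.

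Assessment comes next: "Model performance will be estimated using five times repeated 10-fold cross-validation and compared with models trained on surrogate data". Tuning uses cross-validated criteria: "Model selection will be done to maximise the Mathews correlation coefficient for dichotomised outcomes", and root mean square error (RMSE) for continuous outcomes. The paragraph explains the lack of a test set by saying that "holding out a subset of data before the analysis to be used as a pseudo-independent test set is impossible".

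The surrogate data set is described as "preserving the descriptive statistics but not any of the potentially real associations between the variables and the outcome of the original dataset", after which "the performance of models trained on the actual and surrogate dataset will be compared". The text does not say whether the surrogate is built from all variables and filtered afresh, or only from the variables already chosen on the real outcome.

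**The concern.** Cross-validation gives a fair estimate only if nothing about a test fold's outcomes has been used to build the model tested on it. Here the filter uses the outcomes of all patients, and nothing in the paragraph returns it to the training folds. Variables that correlate with the outcome by chance in the full sample are kept, and the same chance correlation then helps them in each test fold.

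With no hold-out set, cross-validation and the surrogate comparison are the only internal checks. The performance metrics and their confidence intervals inherit the bias. So does the MARS importance ranking, which is defined as the loss of cross-validated performance when a predictor is removed. At stake is the second aim of the study: which variables are named as the strongest predictors, and how well they appear to predict.

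**Working it through.** **The plan's own figure.** Under Predictor profiling the article gives 81% power for an effect size of 0.5, with 54 persistent and 126 resolved cases less 15% attrition.
- Group sizes: 54 × 0.85 = 45.9, about 46; 126 × 0.85 = 107.1, about 107; total 153.
- Normal approximation: 0.5 × √(46 × 107 / 153) − 1.96 = 0.5 × 5.672 − 1.96 = 0.876, and Φ(0.876) = 0.81.

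The figure reproduces. It concerns a single comparison and does not bear on the leak, but it supplies the sample size for the check.

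**Inputs to the check.**
- From the article: 153 patients, 46 with persistent pain; MARS and trees; 10-fold cross-validation; tuning on the Matthews correlation coefficient (MCC) or RMSE.
- Assumed, because the article gives no figure: 50, 100 or 200 candidate predictors; a filter at p<0.05; pruning at |r|<0.5; independent normal predictors.
- Simplifications: an additive version of MARS; two repeats of cross-validation instead of five; AUC in place of the planned precision-recall area. There were 160 simulated data sets per setting.

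No predictor had any relation to the outcome. By chance about p × 0.05 variables pass the filter: 2.5, 5 and 10 expected. The simulated means for 50 and 200 candidates were 2.7 and 10.1.

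**Filter before cross-validation against filter inside each training fold, pure noise:**

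| Metric | Candidates | Filter before | Filter inside |
|---|---|---|---|
| MARS AUC | 50 / 100 / 200 | 0.59 / 0.62 / 0.59 | 0.49 / 0.50 / 0.49 |
| MARS MCC | 50 / 100 / 200 | 0.12 / 0.17 / 0.14 | 0.04 / 0.05 / 0.04 |
| Tree MCC | 50 / 100 / 200 | 0.15 / 0.17 / 0.17 | 0.05 / 0.07 / 0.05 |
| MARS R² (from RMSE) | 50 / 100 / 200 | +0.02 / +0.01 / −0.03 | −0.05 / −0.07 / −0.09 |

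- MCC was above zero in 84-99% of noise data sets with the filter first, against 61-71% with it inside. The small positive MCC that remains inside the folds comes from tuning and reporting on the same cross-validation.
- R² was above zero in 28-71% of data sets for MARS and 24-44% for trees with the filter first, against 8-17% with it inside.
- Plain accuracy rose from 0.64-0.68 to 0.68-0.70. The majority rate is 107 / 153 = 0.70. The planned binomial test against that rate gave p<0.05 in about 1% of data sets or fewer.

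**Surrogate comparison.** The table shows how often a noise data set, filtered before cross-validation, beat the 95th percentile of surrogates made by permuting the outcome (nominal 5%) when the surrogate was not refiltered:

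| Metric | 50 / 100 / 200 candidates |
|---|---|
| MARS AUC | 51 / 57 / 44% |
| MARS MCC | 22 / 37 / 34% |
| Tree MCC | 27 / 25 / 26% |
| MARS R² | 44 / 29 / 16% |
| Tree R² | 12 / 11 / 6% |

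When the filter was rerun on each surrogate, the rates were 1-11%, about nominal.

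**The case against.** Four objections carry weight.

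1. **Noise would not look predictive on every metric.** A reader might infer that the plan will report skill from pure noise throughout. The check does not support that. Accuracy stays at or below the majority rate. R² stays near zero, and the section on outcome measures makes the continuous outcomes the main scale for analysis, with dichotomisation kept for presentation. The clear inflation is in MCC and AUC; MCC applies only to dichotomised outcomes, and AUC is not a metric that the plan names. A least-squares model fed every filtered variable gives far larger values (AUC up to 0.77, R² up to 0.17), but that is not a planned learner, and the simplified MARS and trees did not reproduce them.

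2. **The surrogate may be sound.** A reader might infer that the benchmark must fail. The article does not say that the surrogate is made after filtering. It speaks of a surrogate of the original data set, which can be read as the unfiltered set. Put through the whole pipeline, the surrogate would expose the leak. This stands, so the surrogate point is conditional. Even then, the reported performance and its intervals stay optimistic.

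3. **An article condenses the full plan.** The number of surrogates and the nesting of the tuning may be fixed elsewhere, and their absence is not held against the article. The order of filter and cross-validation is different, because the article states it.

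4. **This part is exploratory.** Predictor profiling says so and disclaims a clinical tool. That lowers the consequence, not the bias. The same section rests the adequacy of the sample size partly on robust assessment of model performance, and the results are meant to inform later validation studies.

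Two further inferences are not pressed. Leakage through imputation is possible, but imputation is conditional and its effect was not quantified. The text also does not say that the univariate filter is linear.

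**Conclusion.** The point holds in this form: as written, the outcome-based filter precedes cross-validation and no hold-out set corrects for it, so the cross-validated performance, its confidence intervals and the MARS importance rankings will be optimistic. In pure noise the shift is about 0.1 in AUC and about 0.1 in MCC. MARS R² moves from between −0.05 and −0.09 to between +0.02 and −0.03. Plain accuracy does not pass the majority rate. The surrogate comparison gives false positives in 6-57% of data sets if the surrogate skips the filter, and at about the nominal rate if it repeats it.

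The direction follows from the stated order of steps. The size depends on the assumed number of candidates, filter threshold and independence of predictors, and on the simplified learners. Because the analysis is labelled exploratory, this should be fixed before analysis; it does not invalidate the study.

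**What to change.** In the prediction paragraph of the Data analysis plan:

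- State that the univariate filter, correlation pruning and tuning, and imputation if used, are refitted within each training fold. This means nested cross-validation: the inner loop selects and tunes, and the outer loop reports.
- Alternatively, drop the outcome-based filter and rely on the selection built into MARS, refitted in each training fold, with tuning still confined to an inner loop.
- State that many surrogate data sets are generated and that each passes through the identical full pipeline, including the filter.

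No new data are needed. The cost is a change of wording and more computing time. The reported performance will be lower, but free of this optimism.

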#### Predictor profiling

FORECAST aims to identify prognostic factors (the first step in the PROGRESS framework)^78^ rather than developing a clinical prognostic tool or individual risk model which requires much larger sample sizes. We will use robust algorithms that include feature selection, and we will assess model performance using methods developed for small data sets and robust metrics. As this part is an exploratory analysis that could shape future hypotheses and validation studies, our sample size is adequate. Given the anticipated sample size ratios with chronic (180×30%=54) and resolved sciatica (180×70%=126) and accounting for 15% attrition (see feasibility study), we will be able to identify moderate effects (effect size=0.5) using a two-tailed Wilcoxon-Mann-Whitney test (power 81%, alpha 0.05).

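### Multiple imputation, if used, comes before cross-validation, so held-out performance can be inflated by values built from whole-data associations

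*Protocol article*

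**What the plan says.** All of the following comes from the Protocol article, section Data analysis plan, unless stated otherwise.

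- Missing data are dealt with in preprocessing: "During preprocessing, missing data will be examined, the mechanism of missingness will be inferred using hypothesis testing". The inspection includes the outcome, since missingness is also "visually assessed using a matrix of boxplots for all pairs of variables and the outcome".
- Imputation is conditional: "if appropriate, multiple imputation by chained equations will be used". The variables to be imputed, and whether the outcome enters the imputation model, are not listed.
- Validation follows: "Model performance will be estimated using five times repeated 10-fold cross-validation and compared with models trained on surrogate data". The section rules out a hold-out set because the data set is small.
- The surrogate data set is described as "preserving the descriptive statistics but not any of the potentially real associations between the variables and the outcome of the original dataset". The text does not say whether it is made before or after imputation, how many are made, or what counts as outperforming it.
- For continuous outcomes, models are chosen "to minimise the root mean square error for continuous outcomes during cross-validation".
- Sample size estimation, Predictor profiling, allows for 15% attrition. The Magnetic resonance neurography section scans only 100 of the 180 patients.

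**The concern.** Cross-validation is honest only if nothing about a held-out patient has been built with information that the test is meant to withhold. Imputing once on the full data set can break this in two ways.

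1. An imputed outcome is a draw from a regression of outcome on predictors, fitted to all patients with observed outcomes. That regression carries the sample's chance associations. When such a patient is held out, the model gains credit for reproducing the imputation model.
2. A missing predictor in a held-out patient may be imputed with the help of that patient's own outcome.

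A surrogate made by permuting the outcome after imputation loses these built-in associations while the real data keep them, so the comparison tilts towards the real data. With no hold-out set, the cross-validated metrics and the surrogate comparison are the plan's main evidence that the predictors carry information. The importance ranking for multivariate adaptive regression splines (MARS) uses loss of cross-validated performance, so it shares the bias. Tree importance uses node impurity and is not affected by this route.

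**Working it through.** **Inputs from the article.** 180 patients; 15% attrition, so 0.15 × 180 = 27 outcomes missing and 153 observed; 10-fold cross-validation repeated five times; RMSE for continuous outcomes; MARS and decision trees; 100 of 180 scanned, so 80/180 = 44% missing by design if imaging variables are used as predictors.

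**The plan's own figure.** The only number for this analysis is 81% power (effect 0.5, 54 v 126 patients less 15%, two-sided 0.05). Group sizes after attrition are 54 × 0.85 ≈ 46 and 126 × 0.85 ≈ 107. The standard error is √(1/46 + 1/107) = 0.176, so z = 0.5/0.176 − 1.96 ≈ 0.88 and power is 81%. With the Wilcoxon efficiency factor 3/π it is 79%. The figure is reproduced. The article gives no rate at which noise would beat the surrogate, so this was simulated.

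**Common set-up.** The outcome is independent of all predictors. Imputation is Bayesian linear regression (chained where predictors are also missing), with missingness completely at random. Noise beats the surrogate when its cross-validated error is lower than that of one outcome-permuted surrogate, so chance is 50%. This criterion, the number of predictors and the share of missing predictor values are assumptions.

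**A. Linear learner on the five strongest predictors.** Selection is inside the folds, 27 outcomes are missing, and there are five imputations.

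| | 20 predictors | 50 predictors |
|---|---|---|
| Imputed before cross-validation: r | +0.055 | +0.077 |
| Imputed in folds, observed outcomes scored: r | −0.03 | −0.015 |
| Difference | 0.085 | 0.092 |
| Noise beats surrogate, imputed before | 73% | 77% |
| Noise beats surrogate, in folds | 44% | 54% |

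Two further runs of this set-up gave 72% and 73% (20 predictors) and 75% and 75% (50 predictors) when imputing before, against 46% to 51% in folds. In one of these, noise also beat the mean predictor in 13% / 9% of studies when imputed before, against 0.8% / 0.2% in folds.

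**B. Depth-3 tree / MARS-like model.** 27 outcomes and 10% of predictor values are missing unless stated. There are 150 to 300 studies per row, so the Monte Carlo standard error is about 3 to 4 points. The surrogate is permuted after imputation unless stated.

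| Setting | No prior outcome filter | With the plan's univariate filter |
|---|---|---|
| No missing data, 40 predictors | 49% / 48% | 52% / 49% |
| One imputation, 20 predictors | 60% / 55% | 52% / 56% |
| One imputation, 40 predictors | 62% / 65% | 48% / 59% |
| One imputation, 80 predictors | 58% / 79% | 39% / 55% |
| Five imputations, 40 predictors | 68% / 75% | 50% / 65% |
| Five imaging-type predictors 44% missing (others 5%), three imputations, 40 predictors | 71% / 75% | 57% / 71% |
| Only outcomes imputed, 40 predictors | 57% / 56% | not run |
| Only predictors imputed, 40 predictors | 55% / 55% | 47% / 51% |
| Surrogate built from observed outcomes and re-imputed, 40 predictors | 55% / 53% | 43% / 45% |
| Imputed before, observed outcomes scored only, 40 predictors | 52% / 49% | not run |

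**Is scoring observed outcomes enough?** It brings the surrogate comparison in B close to chance. In set-up A, however, whole-data imputation scored on observed outcomes still gave r = +0.01 / +0.03, against −0.03 / −0.015 in folds. A residual of about 0.04 to 0.045 remains, so fitting within folds is not redundant.

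**The case against.** The strongest reply is that the article commits to little. Imputation is conditional, the variables are not named, and fold-level detail is often left to a fuller plan. The power calculation treats patients lost to follow-up as lost: keeping all 54 and 126 would give about 85% to 87%, not 81%. That suggests outcomes might not be imputed at all, although it concerns the Wilcoxon test and does not settle the modelling. The surrogate could also be built from the observed data and passed through every step, in which case most of the excess disappears. The work is declared exploratory.

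Much of this stands. A reader might infer that the plan imputes the outcome and that noise would beat the benchmark in about three of four studies. The documents support neither. Outcome imputation and the timing of the surrogate are not stated. Rates near 75% come from the linear learner, which matches the linear imputation model and is probably a favourable case for leakage, or from the MARS-like model in unfavourable settings. Chance is already 50%. In one linear run a control without missing data beat its surrogate in 57% of studies, so the excess there may be only 15 to 18 points (72 − 57, 75 − 57).

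What does not stand is that nothing needs changing. The article does name a stage for imputation, and that stage precedes the folds. Passing the surrogate through the same steps repairs only the relative comparison; RMSE, accuracy and their intervals would still be computed on any imputed outcomes.

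**Conclusion.** The concern holds in a limited form. Followed as written, the plan allows imputed outcomes, or predictors imputed with the outcome, into held-out scoring, and this biases cross-validated performance upwards. The surrogate comparison is biased as well if the surrogate is made after imputation.

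The size is not fixed by the plan. Under a pure null, noise beats one surrogate in about 40% to 80% of studies: about 73% to 77% with the linear learner and five imputations, about 55% if only predictors are imputed (within two Monte Carlo standard errors of chance), and near 50% if the surrogate is re-imputed. The inflation in cross-validated correlation is at most about 0.09. These figures rest on normal data, values missing completely at random, assumed predictor counts and a MARS-like approximation.

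The univariate filter on the outcome is a separate leak. With 40 predictors and no missing data, it alone made the MARS-like model look better than the mean in 15% of null studies, against 0.5% without it. Adding imputation raised this to 40%.

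Priority is moderate: the analysis is exploratory, but its results are meant to guide later validation work.

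**What to change.** In the Data analysis plan, state that:

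- any imputation model is fitted within each training fold, on training patients only;
- missing predictors of held-out patients are imputed from that model without using their outcome;
- RMSE, the Matthews correlation coefficient and all other performance metrics are computed only on patients whose 3- or 12-month outcome was observed;
- surrogate data sets go through the same impute-then-train sequence.

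Whole-data imputation that includes the outcome can remain for the univariate coefficients and confidence intervals.

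The cost is wording and computing time: 5 × 10 = 50 training folds per model and outcome, each with its own imputations. Performance will rest on about 153 patients instead of 180 and will look slightly less favourable. No new patients or data are needed.
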